### Intervention and grouping

PSCI patients will be randomly assigned to the MAG, ACU, or SHM group. The stimulation target in all groups is the PC6 acupoint (unilateral, right side), located according to the WHO Standard Acupuncture Point Locations on the anterior forearm, between the tendons of the palmaris longus and flexor carpi radialis, approximately 2 B-cun proximal to the palmar wrist crease (Figure 2B). Each group will receive 15 treatment sessions (once daily, 5 days per week for three consecutive weeks).

**Figure 2 fig2:**
[figure not shown]
Three specific intervention methods. **(A)**, PC6 magnetic stimulation; **(B)**, PC6 localization and acupuncture at PC6; **(C)**, PC6 sham magnetic stimulation.

Across all groups, high-frequency rTMS will be administered over the L-DLPFC concurrently with each session of the assigned intervention. This protocol is designed to reflect the “central regulation + peripheral input” rehabilitation model and to ensure ethical consistency across treatment arms. In addition, all patients will receive conventional rehabilitation delivered by a multidisciplinary team in accordance with the Adult Stroke Rehabilitation Guidelines (NICE NG236) (30). This includes physical therapy, occupational therapy, and speech and language therapy, provided for at least 3 h per day, on at least 5 days per week, tailored to individual goals and needs. Rehabilitation also encompasses swallowing assessment and management, prevention of complications, and support for cognitive, psychological, and functional recovery, as outlined in the guideline recommendations for comprehensive stroke rehabilitation. We will document the type, frequency, and duration of conventional rehabilitation received by each participant. If a specific intervention within conventional rehabilitation is likely to influence a patient’s cognitive level, the investigator will document its type, duration, and intensity in detail in the Case Report Form form. Therefore, we will systematically document lesion side (left/right) and key lesion features (e.g., location and volume where available).

#### rTMS over L-DLPFC procedure

rTMS will be performed using a MagNeuroR470 magnetic stimulator (Nanjing Weisi Medical Technology Co., Ltd.), equipped with a double-cone coil and a figure-of-eight coil. The MAG group and SHM group will utilize a paired-pulse mode. For L-DLPFC localization, the “5-cm rule” (31) will be adopted, and the double-cone coil will be vertically positioned to cover the target cortex. To enhance targeting reproducibility and provide auditable documentation, we strengthened cap-based quality control and recording procedures: the target point will be identified on a fitted 10–20 cap and marked at baseline for replication across sessions; cap landmarks (nasion–inion and preauricular points) will be checked at each session; coil orientation/positioning will follow a predefined SOP; coil placement and deviations will be documented. In addition, we will record the target location relative to 10–20 landmarks (e.g., the marked scalp coordinate) to enable protocol adherence auditing across sessions and participants. To ensure consistency and reproducibility across all participants and sessions, all operators will undergo standardized training on coil positioning and stimulation procedures, and a strict, documented protocol will be followed for every stimulation session. Stimulation parameters: high frequency of 10 Hz, intensity of 80% of the resting motor threshold (RMT). RMT will be determined via stimulation of the abductor pollicis brevis muscle on the affected side. Each session will consist of 1,000–1,500 pulses.

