### Inclusion criteria

Aged 30–75 years, right-handed;Definite history of stroke, with clinical and imaging evidence supporting the diagnosis;Presence of impairment in one or more cognitive domains, with a MoCA score <26;Stable vital signs;Written informed consent from the patient or legal guardian.

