##### RMT measurement

RMT will be measured before treatment, defined as the minimum TMS intensity that induces a motor evoked potential (MEP) with a peak amplitude greater than 50 μV in the target muscle at rest in at least 5 out of 10 consecutive trials (32). Subjects will be seated in a stable wooden chair and instructed to remain relaxed but awake throughout the procedure. Recording and reference electrodes will be attached to the muscle belly and tendon of the affected abductor pollicis brevis muscle, respectively, with the ground electrode attached to the dorsum of the ipsilateral hand; inter-electrode spacing will be approximately 2 cm. Patients will be fitted with a positioning cap designed according to the 10–20 electroencephalogram (EEG) system for assisted localization. The figure-of-eight coil will be tangentially fixed to the C3 position on the positioning cap, above the M1 motor area of the dominant hand. Single-pulse stimulation will be initiated at a higher intensity. When 5 out of 10 single-pulse stimulations elicit MEP amplitudes > 50 μV, the stimulator intensity at that point will be defined as RMT (33).

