### Statistical analysis

#### Clinical data analysis

All analyses will be performed using SPSS 26.0 (IBM, Armonk, NY, USA) with two-tailed tests (*p* < 0.05). Quantitative data will be expressed as mean ± standard deviation. Within-group comparisons will use paired t-tests. Between-group comparisons will employ one-way ANOVA or nonparametric rank-sum tests (Kruskal-Wallis test), depending on data distribution. Count data will be presented as numbers (percentages), to be analyzed by *χ*^2^ tests, Fisher’s exact tests, or Ridit analysis. Repeated-measures ANOVA with Greenhouse–Geisser correction will be applied to evaluate longitudinal changes across timepoints. Both intention-to-treat (ITT) and per-protocol (PP) analyses will be conducted. In the ITT analysis, missing outcome data will be handled using multiple imputation under the assumption of missing at random. For the primary outcome (MoCA), we will report effect sizes and 95% confidence intervals for between-group differences in score changes. Clinical relevance will be interpreted using published MoCA change ranges and distribution-based benchmarks, rather than a prespecified minimal clinically important difference (MCID). Pearson’s or Spearman’s correlation coefficients (selected based on data distribution) will be calculated to examine associations between clinical scales and neuroimaging parameters. Covariates including age, sex, years of education, time from stroke onset to study enrollment, and a quantitative metric capturing the “dose” of conventional rehabilitation (derived from documented type, frequency, and duration), and lesion side (left/right) will be incorporated into a multivariate linear regression model evaluating the primary endpoint (change in MoCA score) and key secondary cognitive outcomes. Furthermore, to explore the potential modifying effect of lesion side on treatment response, we will conduct an exploratory analysis by adding a Group × Lesion Side interaction term to the primary multivariate model for the MoCA change score and key imaging outcomes. These interaction analyses will be explicitly labeled as exploratory, and their results will be interpreted cautiously due to the limited statistical power for detecting interaction effects.

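### Motor threshold is recorded from the affected thumb muscle but the coil is fixed at C3 for the dominant hand, so the dosing rule contradicts itself in right-hemisphere strokes

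*Protocol article*

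**What the plan says.** All references are to the protocol article.

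- **Muscle.** rTMS over L-DLPFC procedure: "RMT will be determined via stimulation of the abductor pollicis brevis muscle on the affected side". RMT measurement repeats this for the electrodes, which go on the "muscle belly and tendon of the affected abductor pollicis brevis muscle".
- **Coil.** RMT measurement has the figure-of-eight coil "fixed to the C3 position on the positioning cap, above the M1 motor area of the dominant hand". No alternative position is given.
- **Handedness.** Inclusion criteria: "Aged 30–75 years, right-handed".
- **Lesion side.** Neither the inclusion nor the exclusion criteria restrict the hemisphere. Intervention and grouping says "we will systematically document lesion side (left/right) and key lesion features", and Clinical data analysis uses lesion side as a covariate and plans an exploratory analysis by "adding a Group × Lesion Side interaction term to the primary multivariate model".
- **Use of the threshold.** L-DLPFC rTMS is given at 80% of it in all three arms. In the MAG arm it also sets the starting intensity at PC6, which is then raised until the fingers flex slightly.

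**The concern.** A motor threshold obtained from one hemisphere is read from the opposite hand. With the coil over the left motor cortex, the muscle to record is in the right hand. The protocol fixes the coil on the left for everyone but lets the recorded hand follow the stroke. In patients whose left hand is affected, coil and electrodes do not belong together.

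The operator then has three options: move the coil to C4, move the electrodes to the right hand, or persist with a mismatched pair. The article does not say which, and the choice could vary between operators and patients. It fixes the intensity of the background treatment that the design aims to hold constant. Because the ambiguity falls on one lesion side only, the way the threshold was obtained may vary together with lesion side, and a Group × Lesion Side finding would be harder to explain.

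**Working it through.** The plan gives no figure to reproduce. The check is to follow the written procedure for each lesion side.

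**Step 1: which hand C3 serves.** RMT measurement places C3 over the motor area of the dominant hand. All participants are right-handed, so this is left M1 and the right hand.

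**Step 2: follow the instructions.**

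| Lesion | Affected hand | Electrodes as written | Coil as written | Hand driven from C3 | Compatible? |
|---|---|---|---|---|---|
| Left hemisphere | Right | Right thumb | C3 | Right | Yes |
| Right hemisphere | Left | Left thumb | C3 | Right | No |

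**Step 3: the threshold definition.** RMT measurement defines the threshold by responses above 50 μV in the target muscle in five or more of ten trials. In the second row the recorded muscle is not the one the stimulated cortex drives, so the threshold cannot be validly obtained as defined.

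**Step 4: another reading.** If the affected side meant the side of the lesion, the electrodes would be on the left hand in left-hemisphere strokes, and the conflict would move there. Under either reading one lesion side cannot be handled as written.

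**Step 5: look for a repair elsewhere.** No section gives a C4 position or an unaffected-hand rule. The standard operating procedure mentioned under rTMS over L-DLPFC procedure concerns coil orientation and positioning; nothing says that it settles which hand supplies the threshold.

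**Step 6: how many participants.** Inputs: 105 participants, 35 per arm (Sample size). The proportion *p* of right-hemisphere strokes is not given and is assumed.

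- Participants with conflicting instructions = *p* × 105; expected per arm = *p* × 35.
- Each 10 percentage points: 0.10 × 105 = 10.5 overall; 0.10 × 35 = 3.5 per arm.
- *p* = 0.20: 0.20 × 105 = 21 overall; 0.20 × 35 = 7 per arm.
- *p* = 0.80: 0.80 × 105 = 84 overall; 0.80 × 35 = 28 per arm.

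Under the reading in Step 4 the count is (1 − *p*) × 105, which spans the same 21 to 84.

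**Step 7: dose.** The documents give no threshold values by hand or hemisphere, so neither the size nor the direction of a dose difference can be derived.

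**The case against.** The contradiction in the wording is hard to dispute; the case on the other side is that little follows from it.

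- **A mismatched pair would show itself.** With the left thumb recorded and C3 stimulated, the likely outcome is that the response criterion is not met, not that a wrong value is silently accepted. This is fair. The practical result is an unspecified choice by the operator rather than a known wrong dose.
- **A corrected rule does not remove every link with lesion side.** With C3 and the right hand in everyone, the threshold comes from the lesioned hemisphere in left strokes and from the intact one in right strokes. With a C3/C4 rule, it comes from the hemisphere opposite the L-DLPFC target in right strokes. This stands: dosing by motor threshold in unilateral stroke carries some dependence on lesion side. A single rule removes only the further variation from operators choosing differently, but that part is avoidable.
- **An article condenses, and detail may sit in the operating procedure.** A missing fallback alone would be no finding. Here, however, the article states the muscle, the electrode site and the coil position, and these conflict. If an unseen document has the right rule, the published text still misstates it.
- **The stakes are modest.** The interaction is labelled exploratory, lesion side is already a covariate, and the MAG starting intensity is titrated afterwards. All true, and this limits the weight of the point.
- **It is not certain which word is wrong.** Right PC6, the left DLPFC target and C3 all point to the right hand and left hemisphere, which makes the affected hand the likelier error. But that instruction appears twice, so C3 could be the slip. The authors must decide.

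**Conclusion.** The concern holds. The rule that sets the rTMS intensity in all three arms cannot be followed as written in right-hemisphere strokes. For an assumed right-hemisphere share of 20% to 80%, the instructions conflict for 21 to 84 of 105 participants (7 to 28 per arm). This rests on the affected hand being opposite the lesion, and it does not count patients given a wrong dose.

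The same text governs every arm, so the expected bias in the randomised comparison is none, and group contrasts within a lesion side remain valid. The cost is avoidable variation in the background dose and a less interpretable exploratory interaction. It should be fixed, but it does not threaten the primary analysis.

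**What to change.** In both rTMS over L-DLPFC procedure and RMT measurement, replace the affected abductor pollicis brevis with the right one, keeping the coil at C3 for all participants. This takes the threshold from the hemisphere that holds the L-DLPFC target and agrees with the right-sided PC6 site.

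If the clinical team does intend the affected hand, state instead that the coil goes to C3 when the right hand is affected and to C4 when the left is.

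Under either rule, apply it identically in all arms and record the hemisphere and muscle used for each participant. It would be sensible at the same time to say what is done when no response can be elicited.

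The cost is a wording correction in two sections and one case report form field for hemisphere and muscle. Design, sample size and analysis are unchanged.

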##### RMT measurement

RMT will be measured before treatment, defined as the minimum TMS intensity that induces a motor evoked potential (MEP) with a peak amplitude greater than 50 μV in the target muscle at rest in at least 5 out of 10 consecutive trials (32). Subjects will be seated in a stable wooden chair and instructed to remain relaxed but awake throughout the procedure. Recording and reference electrodes will be attached to the muscle belly and tendon of the affected abductor pollicis brevis muscle, respectively, with the ground electrode attached to the dorsum of the ipsilateral hand; inter-electrode spacing will be approximately 2 cm. Patients will be fitted with a positioning cap designed according to the 10–20 electroencephalogram (EEG) system for assisted localization. The figure-of-eight coil will be tangentially fixed to the C3 position on the positioning cap, above the M1 motor area of the dominant hand. Single-pulse stimulation will be initiated at a higher intensity. When 5 out of 10 single-pulse stimulations elicit MEP amplitudes > 50 μV, the stimulator intensity at that point will be defined as RMT (33).

#### Group-specific interventions

##### MAG group

Patients will receive peripheral magnetic stimulation at the PC6 acupoint(Figure 2A). A figure-of-eight coil (outer diameter: 114.8 mm, inner diameter: 79.6 mm) will be used to deliver peripheral magnetic stimulation. The stimulation frequency will be 20 Hz (high frequency), with intensity gradually increased from 80% RMT until slight flexion of the index and middle fingers is observed. The total stimulation duration per session will be 24 min.

##### ACU group

Patients will receive manual acupuncture at the PC6 acupoint (Figure 2B). All acupuncture procedures will be performed by the same two acupuncturists with over 6 years of clinical experience, who have completed clinical operational training organized by the research team. Following routine disinfection of the local skin at the acupoint, sterile disposable stainless-steel filiform needles (0.25 mm × 40 mm) will be inserted. And lifting-thrusting and twirling techniques will be applied to achieve deqi. Needle manipulation will be performed once every 10 min to maintain needle sensation, with a total of two manipulations, and the needles will be retained for 30 min.

##### SHM group

Patients will receive sham peripheral magnetic stimulation at the PC6 acupoint (Figure 2C). A figure-of-eight coil will be used, with the stimulation frequency set to 0 Hz and intensity set to 0. The coil will be positioned with its non-active (reverse) side facing the skin to ensure that no magnetic field is delivered to the median nerve. However, the auditory output of the device will be identical to that of the active stimulation to maintain blinding (34). The stimulation procedure, including coil placement, duration, and pulse protocol structure, will be identical to that used in the MAG group.

### Outcomes

#### Primary outcome measurement

This study will use changes in Montreal Cognitive Assessment (MoCA) scores before and after treatment as the primary outcome measure. The MoCA is a comprehensive cognitive assessment tool that covers seven domains (visuospatial/executive function, naming, attention, language, abstraction, delayed recall, and orientation). The total score is 30, with a cutoff value of 26. A score below 26 indicates cognitive impairment, and the lower the score, the poorer the cognitive ability (35).

#### Secondary outcomes

Secondary endpoints comprise global cognition, functional independence, anxiety, depression, and sleep quality, each assessed with a validated instrument as detailed below.Mini-Mental State Examination (MMSE): the 30-item MMSE assesses orientation, immediate recall, attention/calculation, delayed recall, language, and visuospatial ability. Education-adjusted cut-offs are ≤17 (illiterate), ≤20 (primary education), and ≤24 (≥junior-high); lower scores denote more severe impairment (36).Modified Barthel Index (MBI): this scale is a specialized tool for evaluating activities of daily living (ADL), comprising 10 assessment items, including eating, bathing, personal hygiene, dressing, bowel and bladder control, bed-to-chair transfer, walking on level ground, wheelchair operation, and ascending/descending stairs. During the assessment, evaluators score each item based on the patient’s level of assistance required. Ten items yield a 0–100 score; lower scores indicate greater ADL dependence (37).Hamilton Anxiety Rating Scale (HAMA): this scale contains 14 items, with 7 items each for somatic anxiety and psychic anxiety. Total scores ≥7 suggest anxiety; higher scores reflect increased severity (38).17-item Hamilton Depression Rating Scale (HAMD): this scale includes 17 items, covering dimensions such as anxiety/somatization, weight change, cognitive impairment, diurnal variation, retardation, sleep disturbances, and feelings of hopelessness. Total scores ≥7 indicate possible depression; higher scores correspond to greater severity (39).Pittsburgh Sleep Quality Index (PSQI): the PSQI consists of 18 items, covering seven components: sleep onset latency, sleep duration, sleep efficiency, subjective sleep quality, sleep disturbances, use of hypnotic medications, and daytime dysfunction. The total score ranges from 0 to 21, with higher scores indicating poorer sleep quality (40).

#### Assessment time

At baseline and at the end of the intervention, all pre-specified outcome measures will be assessed. At the 8-week and 12-week follow-ups, only the MoCA and MMSE will be used.

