**Methods:**

This three-arm randomized controlled trial will enroll 105 patients with PSCI, randomly allocated 1:1:1 to the MAG (*n* = 35), ACU (*n* = 35), and SHM (*n* = 35) groups. Interventions will be administered 5 times/week for 3 weeks. All groups will receive high-frequency rTMS over the L-DLPFC (10 Hz, 80% rest motor threshold). The primary outcome is the Montreal Cognitive Assessment (MoCA) change from baseline to week 3. Secondary outcomes include the Mini-Mental State Examination (MMSE), Modified Barthel Index (MBI), Hamilton Anxiety Rating Scale (HAMA), Hamilton Depression Rating Scale (HAMD), Pittsburgh Sleep Quality Index (PSQI), and adverse events. Functional magnetic resonance imaging (fMRI) and functional near-infrared spectroscopy (fNIRS) data will be acquired at baseline and post 3-week treatment. Clinical data will be analyzed via SPSS 26.0 using repeated measures analysis of variance (ANOVA) to compare intergroup changes in outcomes across time points. Neuroimaging data will be processed in MATLAB R2018a. Correlation analyses will assess associations between clinical scores and neuroimaging parameters.

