**Figure 1 fig1:**
[figure not shown]
Trial flow chart. MoCA, Montreal Cognitive Assessment; MMSE, Mini-Mental State Examination; MBI, Modified Barthel Index; HAMD, Hamilton Depression Rating Scale; HAMA, Hamilton Anxiety Rating Scale; PSQI, Pittsburgh Sleep Quality Index.

**Table 1 tab1:** Details of the planned visit schedule.

Stage	Baseline period	Treatment period			Follow-up period	
TimePoint	0	Week 1	Week 2	Week 3	Week 8	Week 12
Enrollment						
Eligibility screen	×					
Informed consent	×					
Demographic characteristics	×					
Medical history	×					
fNIRS	×			×		
fMRI	×			×		
Interventions						
Magnetic Stimulation Group		×	×	×		
Acupuncture Group		×	×	×		
Sham Magnetic Stimulation Group		×	×	×		
Assessments						
MoCA	×			×	×	×
MMSE	×			×	×	×
MBI	×			×		
HAMA	×			×		
HAMD	×			×		
PSQI	×			×		
Patient safety						
Adverse events		×	×	×		

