### Withdrawal criteria

A participant will be withdrawn from the trial if any of the following conditions occur:Serious adverse reactions requiring termination, as determined by a specialist physician;Worsening symptoms or severe complications necessitating emergency measures;Identification of critical safety concerns by investigators;Voluntary withdrawal for personal, family, or social reasons that precludes completion of the treatment course.

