### Safety assessment

Investigators will be required to monitor and document all adverse reactions in the case report forms (CRFs) according to predefined criteria.

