Moreover, we specifically applied multimodal imaging techniques for objective efficacy evaluation. fNIRS data will be collected at three time points (baseline, immediately after the first session, and after the 15th session) to capture both acute and cumulative effects. The post-first-session scan detects rapid hemodynamic changes that reflect the immediate neuromodulatory impact of a single magnetic- or acupuncture-stimulus, consistent with rTMS-related long-term potentiation (LTP) or inhibition mechanisms (58). This immediate measurement also serves as an early indicator of whether the target brain regions respond to the intervention. The time point after 15 sessions evaluates the cumulative or sustained effects following the full course of treatment. Both neuromodulation and acupuncture may exhibit dose-dependent plasticity effects, where repeated stimulation over days or weeks leads to lasting reorganization of neural circuits and improvements in clinical outcomes (59, 60). Therefore, data collected at the end of the 15-session course can reveal long-term therapeutic effects and changes in brain networks that underlie sustained cognitive improvements. Most importantly, comparing immediate and long-term changes can distinguish transient physiological responses from enduring neuroplastic adaptations. Resting-state fMRI provides whole-brain network analysis, as well as the reconstruction of cognition-related pathways (e.g., hippocampus-posterior cingulate cortex) (61–63). If magnetic stimulation at the PC6 acupoint has a unique effect, we anticipate that fMRI will capture specific network reorganization patterns in the MAG group, such as enhanced connectivity within the DMN and between the DMN and SN, which aligns with mechanisms of post-stroke cognitive recovery. Furthermore, we plan to correlate imaging metrics with cognitive scores to examine the relationship between brain network changes and clinical outcomes, thereby deepening the understanding of the underlying mechanisms.

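### Adverse events are scheduled only to week 3, so 9 of the 12 trial weeks have no systematic safety collection although patients are seen at weeks 8 and 12

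*Protocol article*

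**What the plan says.** The visit schedule in Table 1 has the columns "TimePoint 0 Week 1 Week 2 Week 3 Week 8 Week 12". Its patient-safety row, "Adverse events", is marked at weeks 1, 2 and 3 and is empty at weeks 8 and 12. The MoCA and MMSE rows are marked at baseline and at weeks 3, 8 and 12.

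The Assessment time section agrees with the table: "At the 8-week and 12-week follow-ups, only the MoCA and MMSE will be used".

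The abstract's Methods paragraph ends its list of secondary outcomes with "Pittsburgh Sleep Quality Index (PSQI), and adverse events", so safety is a declared outcome of the trial.

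The Safety assessment section is one sentence: "Investigators will be required to monitor and document all adverse reactions in the case report forms (CRFs) according to predefined criteria". It names no start, no end and no visit.

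Treatment is given "once daily, 5 days per week for three consecutive weeks", so scheduled adverse-event collection ends with treatment.

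**The concern.** A declared secondary outcome has a collection schedule that stops at week 3, although the same patients attend twice more. The article gives no reason for stopping there. Because Table 1 itself fixes the collection times, this is not a detail that a condensed article has left to a fuller document.

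Two things are at stake.

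- **Safety reporting.** Cognition would be reported to week 12, but systematic safety information would cover only weeks 0 to 3.
- **Reading the follow-up scores.** A recurrent stroke, a seizure or a hospital admission after week 3 could lower MoCA or MMSE at week 8 or 12. The exclusion criteria keep out recurrent stroke and pre-existing epilepsy at entry, but the schedule offers no systematic way to see which follow-up scores come after such an event. The Clinical data analysis section applies repeated-measures ANOVA across time points and imputes missing outcomes under missing at random. If a patient misses a follow-up visit because of an event that has no scheduled record, that assumption becomes harder to examine.

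**Working it through.** **Inputs, all from the protocol article**

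- Last scheduled adverse-event mark: week 3 (Table 1).
- Last scheduled visit: week 12 (Table 1).
- Intermediate follow-up visit: week 8 (Table 1).
- Measures at weeks 8 and 12: MoCA and MMSE (Table 1; Assessment time).

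The article states no figure for safety coverage, so there is none to reproduce. The sample-size inputs play no part here.

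**Coverage**

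- Weeks with scheduled collection: 3 of 12, and 3/12 = 25%.
- Weeks without: 12 - 3 = 9, and 9/12 = 75%.
- The gap by interval: 8 - 3 = 5 weeks before the first follow-up visit, and 12 - 8 = 4 weeks before the second; 5 + 4 = 9.
- If each follow-up visit asked about events since the last contact, the two visits would cover 5 + 4 = 9 more weeks, giving 3 + 9 = 12 of 12 with no added visit.

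**Does another section close the gap?**

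- *Safety assessment.* Read as open-ended, it extends past week 3 and differs from Table 1. Read together with Table 1, collection ends at week 3. The text does not say which is meant. It also speaks of adverse reactions, which does not clearly cover an intercurrent event judged unrelated to treatment.
- *Assessment time.* This concerns outcome measures and does not mention safety. It corroborates the empty cells in Table 1 but does not by itself prohibit recording an event.
- *Withdrawal criteria.* One ground is "Worsening symptoms or severe complications necessitating emergency measures". A severe late event could surface by this route as a withdrawal. Events that do not lead to withdrawal would not.
- *Objectivity in outcome assessment and quality control.* Protocol deviations and concomitant rehabilitation that may affect cognition are documented. Intercurrent medical events are not mentioned.
- *Limitations.* Short follow-up is acknowledged as a limit on conclusions about durability. Ending safety collection at week 3 is neither mentioned nor justified.

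None of these sections places adverse events on the week 8 or week 12 visit.

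**What cannot be calculated.** The article gives no event rate for any period, so the 75% is a share of calendar time, not of events. The number of events that would fall outside the window cannot be derived from the document.

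**The case against.** The strongest reply is that the Safety assessment section already requires documentation of all adverse reactions and has no end date. The empty cells in Table 1 fix when checks are scheduled and do not forbid spontaneous reporting. The CRF and its predefined criteria are not shown. This stands in part. A reader might infer that the trial will hold no safety data at all after week 3, or that a site would have nowhere to enter a late event; the document supports neither. It supports only the absence of scheduled collection, with an unresolved difference between the table and the safety text.

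A reader might also infer two contradictions that are not there.

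- The Withdrawal criteria do not conflict with the schedule, because a physician can withdraw a patient for a complication without a scheduled adverse-event visit.
- The Discussion's statement that "repeated stimulation over days or weeks leads to lasting reorganization of neural circuits and improvements in clinical outcomes" is a rationale for efficacy and mechanism. It says nothing about late harm, and reading delayed adverse events into it would be the reader's own step.

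It can further be said that events caused by stimulation or needling may cluster in the treatment weeks, that randomisation balances unrelated events in expectation, and that ending checks with a three-week intervention is a possible design choice. These are fair and limit the consequence. They do not supply the missing justification, and balance in expectation does not identify which individual follow-up scores were affected.

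**Conclusion.** The point holds as a gap in scheduled collection. Table 1 leaves 9 of 12 weeks (75%) without systematic recording of a listed secondary outcome. The Safety assessment section does not clearly fill the gap, because it has no window and may not reach unrelated intercurrent events. The two places need to be reconciled.

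The consequence is moderate. It touches the safety outcome and the interpretation of MoCA and MMSE at weeks 8 and 12; events in that period may go unrecorded, which is weaker than saying that they will. The primary endpoint at week 3 is unaffected. The conclusion rests on Table 1 being the operative schedule and on the Safety assessment text as printed. It assumes nothing about event rates and does not claim that late harms are expected. The change is worth making because it is cheap and because events not asked about at these visits may be hard to recover later.

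**What to change.** 1. Extend the adverse-event row of Table 1 to weeks 8 and 12.
2. Amend Assessment time so that the follow-up visits comprise MoCA, MMSE and adverse events.
3. State in Safety assessment that collection runs to week 12 and includes intercurrent events whether or not they are thought related to treatment.
4. At each follow-up visit, ask about events since the last contact, naming recurrent stroke, seizure and hospital admission. Ask after the cognitive tests are finished, so that the answers cannot influence the scoring.
5. Report adverse events for weeks 0-3 and weeks 3-12 separately, and flag week 8 and week 12 MoCA and MMSE scores that come after such an event.

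The cost is one more CRF page and a few minutes at two visits that already take place. No visit is added, and the sample size, treatment and primary analysis do not change.
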